#### Primary and secondary objective (how supplemental nurse staffing impacts the level of missed nursing care)

Using bedside observations of care, we will employ a before and after design in 4 intervention hospitals selected from the 12 NEST360 hospitals. Our baseline observations will be conducted in the 4 intervention hospitals before enhancing nurse staffing and additional observations will be performed after 6 months. At the same post-intervention time point observations will be made in a further set of 4 hospitals from the original 12 that have not received the workforce intervention (Fig. 1). Our primary analysis will be the before-and-after within-site comparison, the single time-point observations in the 4 non-intervention sites will serve as an external reference for our 4 intervention hospitals. Data on nurse staffing metrics will be collected for 6 months before the workforce enhancement and in the 6 months leading to the post-intervention assessment in the 4 intervention hospitals. These data will be used to assess whether and to what degree providing additional nurses changes nurse staffing metrics as an indication of intervention fidelity. Similar data on nurse staffing metrics will be collected from the 4 reference hospitals and then data from all 8 hospitals at the post-intervention time point will be used to address our secondary objective of exploring the relationship between nurse staffing metrics and nurse-delivered care.

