#### Outcomes

##### Primary outcome

For our primary objective (how supplemental nurse staffing impacts the level of missed nursing care), our outcome will be the change in the magnitude of missed nursing care, which will be measured as a change in a Nursing Care Index (NCI). The NCI is an unweighted aggregate patient-level score of all the items of care that are delivered to a baby compared with all the items of expected care [17]. A lower NCI score means more care is missed while a higher score means more care is carried out by nurses for the baby.

Missed nursing care is a process measure of the quality of care provided and it might be more sensitive to a change in nursing numbers [14]. Additionally, it is a direct marker of the nursing process and is an early precursor to adverse patient health outcomes [14].

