#### Statistical power

Drawing on prior experience for our primary outcome [17], assuming a 5% improvement in mean NCI scores (SD- 15%), adjusting for clustering with a design effect of 1.5 and setting α and β at 5% and 80% respectively, the minimum sample size for this study will be 213 in each period (pre-intervention and post-intervention). This will be split equally across the 4 hospitals (55 babies in each hospital per period). This will further be split across randomly sampled 12-h weekday and weekend shifts and across illness severity categories (A, B, C) (Fig. 3). In each shift, we will aim to observe 4 co-located babies for the entire duration of the randomly sampled 12-h blocks. This has been deemed logistically feasible based on prior experience using the NCI tool within the same setting [17].

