### Statistical analysis

We will use summary statistics to describe our study's contextual data (e.g., monthly admission numbers, and patterns of diagnosis). To determine if there is a change in the level of missed nursing care across periods (pre-and post-intervention), we will use linear regression analysis with the NCI as the outcome variable and observation period as the main independent variable. Linear regression will also be used to assess the effect of intervention after adjusting for potential confounders such as patient severity category, and observation made on a weekend/weekday. We will report the risk ratios and corresponding 95% confidence intervals. For our secondary objectives, we will use interrupted time series analysis to track changes in the secondary quality indicators.

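### The primary linear regressions of the NCI estimate a difference in means, but the article says risk ratios will be reported

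*Protocol article*

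**What the plan says.** Three sections of the protocol article bear on the primary effect measure.

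- **Primary outcome.** The outcome is the change in missed nursing care, "which will be measured as a change in a Nursing Care Index (NCI"). The index is described thus: "The NCI is an unweighted aggregate patient-level score of all the items of care that are delivered to a baby", set against the items that were expected. A higher score means more care was given. No event and no cut-off is defined.
- **Statistical power.** The sample size is derived "assuming a 5% improvement in mean NCI scores (SD- 15" per cent), and "adjusting for clustering with a design effect of 1.5", giving 213 babies per period.
- **Statistical analysis.** For the comparison of periods, "we will use linear regression analysis with the NCI as the outcome variable and observation period as the main independent variable". Then: "Linear regression will also be used to assess the effect of intervention after adjusting for potential confounders". The sentence straight after these two is "We will report the risk ratios and corresponding 95% confidence intervals". Interrupted time series analysis is introduced only after that, for the routinely collected indicators.

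The Study design section confirms which analysis is primary: "Our primary analysis will be the before-and-after within-site comparison".

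**The concern.** The effect measure named for the primary result is not one that the planned model produces. In a linear regression of the NCI on period, the period coefficient is the mean NCI after the intervention minus the mean before it, in NCI points. A risk ratio is a ratio of two probabilities and needs a different model.

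This is the only sentence in the article that says how the primary effect will be expressed. A reader who takes it literally cannot tell which quantity will be published. An analyst who follows it literally has to depart from the stated model. At stake is the agreement between the planned model, the effect the study was sized for and the figure that will appear as the headline result.

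**Working it through.** **1. Which analysis the sentence governs.** It follows the two linear-regression sentences and precedes the first mention of interrupted time series. No log-link, binomial or Poisson model and no dichotomised NCI is described anywhere in the article. On the order of the text, the sentence refers to the unadjusted and adjusted linear regressions of the NCI.

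**2. What the study was sized on.** Inputs from Statistical power: difference 5, SD 15, alpha 5%, design effect 1.5. The article labels 80% as beta; it is read here as power. Sidedness is not stated; two-sided is assumed.

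- n per period = 2 x [SD x (z for alpha + z for power) / difference]^2
- = 2 x [15 x (1.960 + 0.842) / 5]^2 = 141.3, rounded up to 142
- with clustering: 142 x 1.5 = **213**, the stated figure.

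Other readings do not give 213:

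| Reading | n per period |
|---|---|
| Two-sided, absolute 5-point difference, normal formula | 213 |
| One-sided, otherwise the same | 168 |
| Two-sided, t-based (143 x 1.5) | 214.5 |
| 5% as a relative change, assumed baseline NCI 80 | about 332 |
| 5% as a relative change, assumed baseline NCI 50 | 849 |

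The power basis is thus an absolute difference in mean NCI of 5 points.

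**3. What the planned model delivers.** The period coefficient has the same target, 5 points. At 213 per period its standard error is 15 x sqrt(2 x 1.5 / 213) = 1.78 points, so the 95% confidence interval is about ±1.96 x 1.78 = ±3.5 points.

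**4. Why a ratio cannot be read off that coefficient.** A ratio also needs the baseline level and a direction. The article gives no baseline, so these values are assumed for illustration:

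| Assumed baseline NCI | Ratio of care delivered after a 5-point gain | Ratio of care missed |
|---|---|---|
| 40 | 45/40 = 1.125 | 55/60 = 0.92 |
| 50 | 55/50 = 1.10 | 45/50 = 0.90 |
| 80 | 85/80 = 1.06 | 15/20 = 0.75 |

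The same mean difference corresponds to quite different ratios. The direction also matters, because the hypothesis is framed as less missed care while the NCI counts care given.

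**5. Side by side.** Outcome: change in a score. Power: difference in mean score. Model: linear in the score. Reported measure: risk ratio. The first three agree; only the fourth departs.

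**The case against.** The strongest reply is that this is a slip of wording in a condensed article. Outcome, model and power basis all point to a mean difference, so the intended quantity can be recovered, and the likeliest course is that the analyst reports the regression coefficient. Much of this stands, and it limits the point to one sentence. It does not remove the point: the article does not leave the effect measure to a later document but names one, and the one it names does not fit the model.

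A second reply is that a ratio is not absurd for this outcome. The NCI compares items delivered with items expected, so a ratio of the proportion of care delivered, or missed, is a coherent quantity. That also stands. The fault is a mismatch between model and measure, not an impossible measure. The article does not, however, plan a model that would estimate such a ratio.

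A reader might go further and infer that the analyst is forced either to exponentiate the linear coefficient or to dichotomise the NCI. The first gives exp(5) = 148 on a 0–100 scale and exp(0.05) = 1.05 on a 0–1 scale. The second, with a median split of a normal outcome, would cut power to about 61%: 5/1.78 x sqrt(2/pi) = 2.24, and Phi(2.24 - 1.96) = 0.61. The arithmetic is right, but the documents do not support the inference. Neither step is planned anywhere, and other routes exist, such as a model of item counts or simply reporting the coefficient. The loss of power belongs to an analysis the protocol does not propose and is no cost of this sentence.

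**Conclusion.** Wrong as written. The planned unadjusted and adjusted linear regressions estimate a difference in mean NCI, and the outcome definition and sample size rest on the same quantity; risk ratio is the wrong name for what will be estimated. The sample size of 213 per period, its power of about 80%, the design and the linear model are unaffected.

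This rests on two readings: that the risk-ratio sentence refers to the regressions it follows, and that the 5% and 15% are absolute NCI points. The text order supports the first and the exact reproduction of 213 supports the second. The documents do not support the wider conclusions that the primary result would be uninterpretable or that its outcome would be chosen after the data are seen: the outcome and the model are both stated.

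**What to change.** Replace the sentence with: *We will report the unadjusted and adjusted mean differences in NCI (percentage points, post minus pre) with 95% confidence intervals.* Both estimates should be named, because the section lists the comparison by period alone first and the adjusted one second.

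If a ratio is truly intended, pre-specify instead a model that estimates it, for example a log-link or binomial-type model of items delivered out of items expected, and state whether the event is care delivered or care missed. The link to the power calculation would then need to be explained, since that was done for a difference in means.

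The first option costs one sentence, with no change to data collection, model or sample size. The second changes the primary model and should be chosen only if a ratio is the quantity wanted.

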### Dissemination plan

We intend to present the result of this study to the participating hospitals, relevant stakeholders including the Ministry of Health and professional associations, at conferences and publish them in scientific peer-reviewed journals.

### Confidentiality

Data collected using the study observational checklist (supplementary material) will be kept securely at the KEMRI Wellcome Trust Research Programme (KWTRP) and entered on-site into password-protected computers with encryption using Redcap software. Data from individual deidentified observational checklists will be collated on a central server maintained by the KWTRP after being encrypted for transmission over the internet. De-identified data shared with KWTRP will be stored in secure servers with password-protected access and as guided by KEMRI – Wellcome Trust ICT and Data Management policies. Data held on these servers are backed up in similar password protected mirror servers at another location within the KEMRI – Wellcome Trust.

## Discussion

Both material and human resources are crucial to maintaining the quality of patient care. Interventions to improve in-patient quality of care in resource-constrained settings have largely ignored a critical element for quality service delivery which is having an adequate number of health staff. For example, many interventions focus on enhancing technology or skill acquisition of existing local health workers. Yet, these require the presence of a sufficient numbers of staff to promote optimal effectiveness and ensure patient safety.

To the best of our knowledge, this is the first prospective workforce intervention study that proposes to supplement nurses within a hospital setting to examine the association between improved staffing and quality of care. Previous research has been retrospective, evaluating the effects of improvements in staffing in the form of natural experiments or has involved prospective supplementation of nursing assistants [25–27].

We recognise that the Hawthorne effect is a limitation of studies that involve direct observations [28], and we plan to minimise the effect of this on our data collection. Similar to our earlier work using the NCI tool, before the current data collection, we will conduct training of the observers and have a one-week familiarisation period within our study sites [17]. This period involves observers learning the layout and routines of each unit and this also serves to make the nurses within the units comfortable with the observer. We will spread our data collection across randomly selected 12-h nursing shifts over 5 to 6 weeks that are not known to the nursing staff in advance while evidence also suggests that following the continuous presence of an observer for longer periods, the Hawthorne effect is likely to diminish [29].

## Data Availability

Not applicable.

## Abbreviations

CIN: Clinical Information Network
HIC: High Income Country
HRH: Human Resources for Health
NCI: Nursing Care Index
NEST-360^o^: Newborn Essential Solutions and Technology 360^o^
LMIC: Low-middle Income Country
